#### Providers eligibility criteria:

- Ability to provide informed consent
- Age = 18 yrs. old or older
- Child care teachers only: Be a teacher in a 2-5 year old classroom
- Child care teachers only: Not pregnant, not planning on becoming pregnant, and does not become pregnant during the study

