#### A.3.3. Will pregnant women or women who become pregnant be excluded?

Yes

If yes, provide justification and describe the type and timing of pregnancy testing to be used:

It is not typically recommended that women lose weight during pregnancy. Instead, they encourage pregnant women to focus on getting enough nutrients and exercise to keep themselves healthy. Weight loss in those pregnant or wanting to become pregnant would require additional medical oversight beyond what is proposed in the present study.

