#### A.4.2. Describe the study design. List and describe study procedures, including a sequential description of what subjects will be asked to do, when relevant.

The proposed study will use a cluster randomized control trial to evaluate if improving child care providers' health behaviors elicit meaningful change in dietary and PA behaviors in 2-5-year-old preschool children in their care and the child care environment. To evaluate the impact, measurements will be collected at three-time points baseline, post-intervention (6 months), and maintenance (12 months post, no contact). Measures will be collected using a combination of self-report surveys, direct observation/measurement, and interviews by trained project staff. Additionally, The Go NAPSACC Enhanced arm will include a child care provider-level weight management intervention that encourages a reduced energy diet (stop light diet [SLD]), increased PA, and regular weight monitoring. We will use commercially available applications for self-monitoring PA (Fitbit Inspire 3) and weight (Aria wireless scales).

**Randomization.** Centers will serve as the unit of randomization. Following baseline testing of each center, the study statistician ([name]) will randomize centers to either standard Go NAPSACC or Go NAPSACC Enhanced. Randomization tables will be created by [name] using a permuted block approach, with block sizes of 2-4 to ensure equal distribution between arms throughout the randomization period. [name] will deliver intervention assignments directly to the study coordinator, who will inform participating centers and the Health Educator delivering the intervention. Investigators (except the study statistician) and data collectors will be kept blinded.

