## A.6.10. Describe any potential physical risks checked above, including the category of likelihood and severity, and what will be done to minimize these risks. Where possible, describe the likelihood of the risks occurring, using the following terms:

- Very Common (approximate incidence > 50%)
- Common (approximate incidence > 25 - 50%)
- Likely (approximate incidence of > 10 - 25%)
- Infrequent (approximate incidence of > 1 - 10%)
- Rare (approximate incidence < 1%)

Describe severity of risks using the following grading scale:

- Mild- No disruption to the subject's ability to perform daily activities; may include non-prescription intervention only
- Moderate- Temporary interference with daily activities; may include prescription intervention
- Severe- Interference with daily activities; medically significant but not life threatening
- Life threatening

Examples:

Rare ( < 1%) and Severe: blindness

Rare ( < 1%) and Mild: dry skin, dry mouth, transient headache

If you are using these terms differently than described above, please provide your study-specific definitions.

Phase 1 trials: Due to limited experience, incidence may be better described as the number of events that have occurred in the total number of animals/humans studied.

Increasing one's physical activity, particularly for individuals who are inactive, can be accompanied by some initial discomfort and soreness of muscles. Additionally, injury is possible as the result of participation in physical activity. For adult participants it will be recommended that they consult their primary care physician before making major changes to their physical activity habits.

A.6.11. Unless already addressed above, describe procedures for referring subjects who are found, during the course of this study, to be in need of medical follow-up or psychological counseling

Not applicable.

A.6.12. Are there plans to withdraw or follow subjects (or partners of subjects) who become pregnant while enrolled in this study?

Yes

If yes, explain

It is not typically recommended that women lose weight during pregnancy. Instead, they encourage pregnant women to focus on getting enough nutrients and exercise to keep themselves healthy. Weight loss in those pregnant or wanting to become pregnant would require additional medical oversight beyond what is proposed in the present study.

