#### B. Safety Assessment

- 1. Adverse Events (Table 9)
- 2. Analysis (Table 10 and 11)

A.7.2. If not already addressed above, describe the plans for aggregate review of unanticipated problems (including but not limited to adverse events) across all sites, in order to monitor subject safety.

At enrollment, we will inform child care centers and their participating providers to contact the project manager if they feel an injury or illness may have occurred to them or a child in their care as a result of their participation in this study. If such an event occurs, the project manager will collect a detailed description of the event, the adverse outcome, severity of the adverse event, and whether or not participants viewed it as related to the study. This report will then be reviewed by the DSM officer, who will categorize it as: definitely unrelated, or unlikely, possibly, probably, or definitely related to study participation. Although injuries could occur as a result of an intervention that promotes regular physical activity, in our previous center-based work, no injuries related to participation were reported. We therefore anticipate that injury risk is present, but

minimal.

Adverse event reports will be submitted to the IRB after completion by the DSM officer. The PI will submit a summary of these reports to the NIDDK project officer on an annual basis. As a minimal risk study that complies with all guidelines for data and participant safety, study suspension is not anticipated. However, if such an event were to occur, the Principal Investigator would contact NIDDK immediately to report the suspension, give reasons for the suspension, and describe the plan to meet the requirements for lifting the suspension

A.7.3. What are the criteria that will be used to withdraw an INDIVIDUAL SUBJECT from this study or halt the research intervention (e.g., abnormal lab tests, allergic reactions, failure or inability to comply with study procedures, etc.)?

There are no instances where we would withdraw an individual subject from the study or halt the research intervention.

A.7.4. Are there criteria that will be used to stop the ENTIRE STUDY prematurely (e.g., safety, efficacy, unexpected adverse events, inability to recruit sufficient number of subjects, etc.)?

Yes

Please explain

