Missing data and statistical models. All analyses will be conducted using the intention-to-treat principle (ITT), in which all available data on all randomized participants are included. This approach minimizes bias if individuals drop out of the trial for different reasons. Every effort will be made to obtain follow-up data on all patients randomized, whether or not they follow their assigned treatment. Our maximum likelihood approach assumes that any missing outcome data is missing at random (i.e., missing data including that due to drop-out can be dependent on any previously observed outcomes or treatment assignment). With this approach, we use all data that have been collected without regard to whether data are missing for a patient at another visit, including drop-out, and without explicit imputation of missing data. If the combined rate of missingness on variables is above 5%, we will consider imputing missing endpoint data using multiple imputation techniques and will assess the sensitivity of our results to various assumptions of missing data patterns.

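### The protocol excludes teachers who become pregnant during the study (A.3.1, A.3.3), rules out any withdrawal or halt (A.7.3), and leaves open whether they are withdrawn or followed (A.6.12)

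*Protocol*

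**What the plan says.** Five places in the Protocol bear on a teacher who becomes pregnant after she has enrolled.

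- **A.3.1, provider eligibility (teachers only):** "Not pregnant, not planning on becoming pregnant, and does not become pregnant during the study". The last clause concerns the future, not status at entry.
- **A.3.3:** the question "Will pregnant women or women who become pregnant be excluded" is answered yes. The reason given is that "Weight loss in those pregnant or wanting to become pregnant would require additional medical oversight beyond what is proposed in the present study".
- **A.6.12:** the question "Are there plans to withdraw or follow subjects (or partners of subjects) who become pregnant while enrolled in this study" is answered yes. The explanation repeats the A.3.3 rationale and names no action.
- **A.7.3, criteria for withdrawing an individual:** "There are no instances where we would withdraw an individual subject from the study or halt the research intervention".
- **A.8.1, missing data:** analysis is by intention to treat, "in which all available data on all randomized participants are included", and "Every effort will be made to obtain follow-up data on all patients randomized, whether or not they follow their assigned treatment".

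On timing, A.4.2 places randomisation after baseline: "Following baseline testing of each center". Teachers are then measured at 6 and 12 months for weight, diet quality and physical activity (Aim 2, secondary outcomes).

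**The concern.** Eligibility can be judged only on what is known at entry. Once a center is randomised, a criterion that depends on a later pregnancy removes a randomised participant because of something that happened after allocation. That is hard to square with an intention-to-treat analysis that promises follow-up whatever treatment is received.

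The document also gives staff instructions that cannot all be carried out, and the two main readings fail in different ways. If A.7.3 governs, a pregnant teacher in the Enhanced arm stays in a weight-management program although the protocol itself says that weight loss in pregnancy needs oversight it does not propose. If A.3.1 and A.3.3 govern and mean withdrawal, the A.8.1 follow-up commitment is not kept for her. These are alternatives, and the same teacher cannot suffer both. But the text does not say which applies, so different staff could handle like cases differently.

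**Working it through.** The main check is a comparison of texts. There are three things staff could do when a randomised teacher becomes pregnant. Each is set against the stated rules:

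| Action | A.3.1 / A.3.3 (excluded) | A.7.3 (no withdrawal, no halt) | A.8.1 (follow all randomised) |
|---|---|---|---|
| Withdraw her from the study | met | broken | broken |
| Stop the program, keep measuring her | met only if exclusion means from the program alone | broken | met |
| Continue unchanged | broken | met | met |

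No row satisfies every column. The most sensible action, the second, still breaks A.7.3, because that field rules out halting the intervention as well as withdrawing the person. A.6.12 does not break the tie: its yes covers either withdrawing or following, and its explanation gives a reason without a rule.

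The criterion applies to teachers in both arms. The stated rationale concerns weight loss, and in the standard arm the program is delivered only through directors (A.4.2). So the rationale gives no reason to stop measuring a standard-arm teacher who becomes pregnant.

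**Scale.** The Protocol gives no pregnancy rate, so one has to be assumed.

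- Teachers: 84 centers × 2 = 168 (agrees with A.2.3).
- Number affected over 12 months = 168 × p.
- p = 1%: 168 × 0.01 = 1.7. p = 3%: 168 × 0.03 = 5.0. p = 5%: 168 × 0.05 = 8.4.

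That is about 2 to 8 teachers. An assumed range of 2 to 6% gives 3.4 to 10.1, or about 3 to 10, which is the same order.

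If exclusion were taken to end measurement, which the text does not say, and pregnancies were spread evenly over the year, the follow-up visits affected would be 168 × p/2 at 6 months plus 168 × p at 12 months. Out of 168 × 2 = 336 visits:

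- p = 1%: 0.84 + 1.68 = 2.52, or 0.75%.
- p = 5%: 4.2 + 8.4 = 12.6, or 3.75%.

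This is an upper bound under those assumptions and not a prediction.

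**The case against.** The strongest reply is that A.7.3 is a generic form field, prompted by laboratory abnormalities, allergic reactions and non-compliance, whereas pregnancy has fields of its own. A.3.1, A.3.3 and A.6.12 all point away from business as usual. A pregnant teacher would stay on weight loss only if staff followed the generic line over the three specific ones. The program is also mild: teachers may choose maintenance, the diet sets no specific calorie deficit, and active prompting ends after month 6 (A.4.2). Adults are advised to see their physician before major changes in activity (A.6.10), may stop at any time (A.6.2), and safety officers review reports (A.7.1).

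Much of this stands, and it lowers the practical risk. It does not remove the conflict. A.7.3 is worded absolutely, and none of the specific fields says what is to be done. The diet's stated suitability for all participants uses low BMI as its example and does not mention pregnancy.

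Four stronger readings are tempting and are not supported:

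- A reader might infer that the teacher's later visits are lost. A.3.1 and A.3.3 do not say that outcome collection ends, and A.8.1 could coexist with stopping only the program.
- A reader might infer that her classroom's children leave too, since a child must be in a participating teacher's classroom. That is an entry criterion, and nothing in the Protocol removes a child when a teacher leaves.
- A reader might infer an imbalance between arms or an effect on the primary child outcomes. Nothing in the document shows either.
- A reader might infer that no pregnancy procedure exists anywhere. The teacher consent form and grant application are listed as attachments but are not shown, and either may contain one. That would not cure the wording of A.7.3.

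How weights measured during pregnancy are analysed is ordinary SAP content, and its absence here is no fault.

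**Conclusion.** The point holds as an inconsistency in the protocol's conduct rules. A.3.1 and A.3.3 exclude on an event that can follow randomisation, A.7.3 forbids any withdrawal or halt, and A.6.12 does not choose. An SAP can say how data are analysed, but it cannot tell staff whether to stop a program or keep visiting a teacher.

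The consequences are confined to participant safety in the Enhanced arm and to the secondary provider outcomes. The number affected is unknown. The figure of about 2 to 8 teachers rests wholly on the assumed 1 to 5% rate, and the exclusion of women planning pregnancy may make the true rate low. The correction is worth making because every literal reading breaks at least one stated rule and the remedy is only wording.

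**What to change.** 1. **A.3.1 and A.3.3:** apply the pregnancy criterion at enrolment only (not pregnant and not planning pregnancy at entry), and delete the clause about pregnancy during the study.
2. **A.6.12 and A.7.3:** state that if a teacher becomes pregnant, the weight-loss component is stopped or modified under a clinical rule set by the investigators. State also that she remains, in either arm, in the 6- and 12-month follow-up and in the intention-to-treat set.
3. Leave the handling of weights measured in pregnancy to the SAP.

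Amending only A.7.3 and A.6.12 would remove the direct contradiction. Limiting A.3.1 and A.3.3 to entry is also needed to remove the post-randomisation exclusion.

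The cost is an IRB modification covering four fields, with no added visits. If the teacher consent form states a pregnancy rule, it needs a matching change, and whether the teachers among the 43 subjects already enrolled must re-consent would have to be decided. The same submission reports 0 subjects in the interventional part, so at that date the rule could be set before it was needed.

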#### Child Eligibility criteria

- In a classroom with a participating child care teacher

- 2-5 yrs. old
- Consenting primary caregiver must be able to read English

#### A.3.2. Justify any exclusion based on race, gender or ethnicity

N/A

#### A.3.3. Will pregnant women or women who become pregnant be excluded?

Yes

If yes, provide justification and describe the type and timing of pregnancy testing to be used:

It is not typically recommended that women lose weight during pregnancy. Instead, they encourage pregnant women to focus on getting enough nutrients and exercise to keep themselves healthy. Weight loss in those pregnant or wanting to become pregnant would require additional medical oversight beyond what is proposed in the present study.

### A.4. Study design, methods and procedures

*Your response to the next question will help determine what further questions you will be asked in the following sections.*

#### A.4.1. Will you be using any **methods or procedures commonly used in biomedical or clinical research** (this would include but not be limited to drawing blood, performing lab tests or biological monitoring, conducting physical exams, administering drugs, or conducting a clinical trial)?

Yes

#### A.4.2. Describe the study design. List and describe study procedures, including a sequential description of what subjects will be asked to do, when relevant.

The proposed study will use a cluster randomized control trial to evaluate if improving child care providers' health behaviors elicit meaningful change in dietary and PA behaviors in 2-5-year-old preschool children in their care and the child care environment. To evaluate the impact, measurements will be collected at three-time points baseline, post-intervention (6 months), and maintenance (12 months post, no contact). Measures will be collected using a combination of self-report surveys, direct observation/measurement, and interviews by trained project staff. Additionally, The Go NAPSACC Enhanced arm will include a child care provider-level weight management intervention that encourages a reduced energy diet (stop light diet [SLD]), increased PA, and regular weight monitoring. We will use commercially available applications for self-monitoring PA (Fitbit Inspire 3) and weight (Aria wireless scales).

**Randomization.** Centers will serve as the unit of randomization. Following baseline testing of each center, the study statistician ([name]) will randomize centers to either standard Go NAPSACC or Go NAPSACC Enhanced. Randomization tables will be created by [name] using a permuted block approach, with block sizes of 2-4 to ensure equal distribution between arms throughout the randomization period. [name] will deliver intervention assignments directly to the study coordinator, who will inform participating centers and the Health Educator delivering the intervention. Investigators (except the study statistician) and data collectors will be kept blinded.

#### **Intervention**

**Standard Go NAPSACC.** Centers randomized to standard Go NAPSACC will receive the traditional Go NAPSACC program. Go NAPSACC is grounded in Social Cognitive Theory (SCT), targeting constructs (e.g., expectancies, observational learning, self-efficacy, behavioral capacity, environment, situation, reinforcement, reciprocal determinism) hypothesized to produce changes in the child care environment which foster healthier habits in enrolled children. The implementation model used to support center wide changes focuses on engaging center directors and orienting them to Go NAPSACC, giving access to interactive online tools that guide change, and providing ongoing support as they work to adopt organization-level evidence-based healthy weight practices. More specifically, the 6-mo. implementation model that will be employed in this trial will include:

- Director Engagement and Orientation. The director will sign on to lead the Go NAPSACC effort for their child care center, helping to ensure that changes are applied center wide and not just to specific classrooms. The directors will take part in a 1-hour, video conference orientation. The orientation will be provided by Go NAPSACC's Implementation Advisor using standardized materials, which include a slide presentation with talking points and a user guide. The orientation will instruct center directors on how to use the Go NAPSACC online tools and guide them through the creation of a personalized account. A 6-month timeline will also be provided that offers suggested milestones for completing each of the 5 steps.
- Access to Go NAPSACC Tools. Directors will use their personalized account to access Go NAPSACC's interactive, online tools that guide them through the 5-step improvement process: 1) assess, 2) plan, 3) take action, 4) learn more, and 5) keep it up. **Assess** tools provide self-assessments to help directors reflect on their current practices. **Plan** tools help directors use feedback from their self-assessment to select goals and create customized action plans to reach those goals. **Take action** tools offer a library of tips and materials that help directors as they work through their action plan steps. **Learn more** tools offer trainings to improve knowledge and skills for healthy weight practices. **Keep it up** tools encourage directors to retake the self-assessment to gauge progress and identify areas for future work.
- Ongoing Support. For 6 months, directors will receive monthly check-ins by telephone or email from the Implementation Advisor. Check-ins will be used to encourage directors to complete at least one cycle of Go NAPSACC's 5-step process (using milestones from the 6-mo timeline to guide pace), inquire about progress on goals, troubleshoot technical issues, and support navigation of the tips and materials library and trainings.

No contact follow-up (7-12 months). Centers will continue to have access to the Go NAPSACC online tools and will be encouraged to continue additional cycles of the improvement process; however, the active engagement of centers to provide ongoing support will cease. Because standard Go NAPSACC is delivered solely through interaction with center directors, there will be no direct contact between the research team and children or child care providers, except during data collection (0, 6, and 12 months).

Go NAPSACC Enhanced. Centers randomized to Go NAPSACC Enhanced will receive the traditional Go NAPSACC program (described above); in addition, child care providers will simultaneously receive an evidence-based weight management intervention. The Go NAPSACC Enhanced online tool created for providers will focus on personal weight management strategies. Each provider will have their own account (set up at orientation) through which they will take a self-assessment and choose a goal of weight maintenance or weight loss. Additionally, they will have access to materials that will support their adoption of evidence-based strategies for their weight management or loss goal. These strategies, also guided by SCT, pull from national nutrition and PA behavior recommendations and behavior change strategies that increase intervention adherence and improve weight loss. The intervention integrates techniques known to be most effective for changing diet and PA behaviors, including intention formation, goal setting (e.g., =5% weight loss at 6 months and no regain at 12 months), self-monitoring (diet, PA, weight), and feedback. These techniques will be enhanced by employing behavior shaping (gradually modifying diet and PA), stimulus control (strategies to decrease cues for less desirable and increase cues for more desirable diet and PA behaviors), including cognitive strategies to increase self-efficacy and to deal with social relationships affected by weight, such as identifying/confronting self-sabotage attempts, responding to stress with non-food techniques, and relapse prevention strategies to teach participants to recognize precursors and consequences of lapses, and developing plans for addressing high risk situations. The 6-months weight management intervention will include:

- Child Care Provider Orientation. Child care Providers will take part in a 1-hr., in-person orientation session, where a Health Educator will provide an introduction to Go NAPSACC Enhanced weight management intervention, including an overview of the Go NAPSACC Enhanced website and creation of a personalized account, a description of the self-assessment and choosing a weight management or loss goal, a detailed description of the diet and PA components, a 6-mo timeline with suggested milestones and instructions on self-monitoring devices. All participants will be provided with , a Fitbit Inspire 3™ activity tracker, and an Aria wireless scale (Fitbit, Inc., San Francisco, CA), and time will be allotted for demos, practice, questions, and troubleshooting (e.g., internet connectivity, app data entry). While providing these devices may somewhat diminish future scalability and sustainability, the

standardized devices are required for all participants to ensure connection (syncing Fitbit and wireless scales) and to allow investigators to push remote updates to devices. Participants will have full access to study related materials and commercial apps from their personal smartphones and computers. Any technical issues will be resolved by contacting project staff by phone or email.

- Dietary Modification. The reduced energy diet will follow the SLD approach (previously described) based on weight management goal (loss or maintenance). Starting weight will be used to suggest tailored red food limits: Weight Loss - <250lbs = 3; 250 - <300 = 4; >300 = 5. Weight Maintenance - <250 = 4; 250 - <300 = 5; >300 = 6. The SLD approach is suitable for all participants (including for whom weight loss may not be recommended [e.g., BMI <25 kg/m^2]) as it does not specifically prescribe a calorie deficit but focuses on improvement of diet quality.
- Physical Activity. We will prescribe a progressive moderate intensity PA program (walking, jogging, biking, etc.) as recommended the "Physical Activity Guidelines for Americans" of 150 min/wk. Starting active minutes goal will be based on self-reported current activity levels: 0 min/wk = 10 min/day goal; 1-59 min/wk = 15/min/day goal, >60 min/wk = 20 min/day goal.
- Self-monitoring. Participants will be asked to self-monitor diet and PA daily, and body weight weekly. This data, which is automatically available to both participants and Health Educator, will be used for participant motivation and accountability, and to inform counseling by the Health Educator. Diet. Participants will log and view their dietary progress on the "Diet" page of the Go NAPSACC Enhanced website, which will include the current day's tally of caloric beverages and red foods, in addition to a graph of totals over time. PA. Participants will wear a Fitbit Inspire 3 wireless activity tracker on their non-dominant wrist. This device tracks PA with minimal participant burden and provides real-time data, via the Fitbit app. Body weight. Participants will be asked to weigh weekly using a Fitbit Aria wireless scale which interfaces with the Fitbit app to provide feedback to both participants and the Health Educator. These non-fasting weights will be used only for participant/Health Educator feedback, not as outcome weights.
- Behavioral lessons. The Go NAPSACC Enhanced website will unlock new modules that will convey the primary lesson objectives weekly during weight loss (0-6 months). Automated notifications of the addition of new modules will be sent to participants, via text message, including a link that opens directly to the Lessons webpage. Lessons will consist of written content focusing on reinforcing weight management strategies, including what strategies look like, why they are important, and practical tips for incorporating them into their everyday lives. Lessons will include topics such as portion sizes, reducing caloric beverages and red foods, emotional eating, behavioral strategies to increase PA, importance of sleep and stress management, stimulus control, sustaining changes, problem solving, and relapse prevention.
- Ongoing support. Participants will receive weekly reminders, via Twilio using encrypted text messaging, to complete self-monitoring. Participants self-monitoring data on diet, PA, and weight will be available immediately, but it will also be used to provide tailored weekly feedback. The weekly tailored feedback will be sent to participants via Twilio and offer congratulations for meeting goals, additional tips for those not meeting goals, or encouragement to monitor behavior for those who do not sync Fitbit and scale data. In addition, participants will also get weekly text messages through Twilio encouraging them to access the lessons (with quick access link). Participants will also receive motivational messages and tips for behavior change at random intervals each week, which has been shown to increase the effectiveness of SMS-based interventions. All messaging through Twilio is encrypted. Twilio encrypts data both in transit and at rest. They support TLS 1.2 to encrypt network traffic between participants and Twilio and Twilio data is encrypted at rest utilizing industry standard encryption algorithms.

Secondary users (any other center staff) from the Go NAPSACC Enhanced arm will have access to the website and its resources. No data will be collected on these users.

No contact follow-up (7-12 mos). Participants will continue to have access to Go NAPSACC Enhanced online tools, self-monitoring devices (i.e., tablet, Fitbit, wireless scale), and previously posted lessons and resources. They will be encouraged to continue self-monitoring diet, PA and weight. We will track the frequency of self-monitoring during the no-contact period; however, feedback from the Health Educator will not be provided and the active engagement of participants via self-monitoring reminders, tailored feedback, and motivational messages will cease.

